#### European Union (EU) requirements for influenza vaccines

The Committee for Medicinal Products for Human Use (CHMP) has defined a set of regulatory criteria influenza vaccines need to meet in order to obtain a marketing license in the European Economic Area (39). The vaccine efficacy is tested by the haemagglutination inhibition (HI) (40 {Kendal, 1982 #224}), or single radial haemolysis (SRH) assays (41). An HI titre  $\geq 40$  (or an equivalent SRH  $> 25\text{mm}^2$ ) indicates 50% protective levels of serum antibody against influenza infection in man. The EU requirements for harmonisation of influenza vaccines require annual clinical trials for licensing. The vaccine should fulfil one of the following evaluation criteria for each strain in adults aged 18-60:

1. The number of seroconversions or significant increases in anti-haemagglutinin antibody titre should be  $> 40\%$ ;
2. Mean geometric increase  $> 2.5$ ;
3. The proportion of subjects achieving an HI titre  $\geq 40$  or SRH  $> 25\text{mm}^2$  should be  $> 70\%$ .

There are no requirements for inactivated vaccines to evoke a cellular immune response. The World Health Organisation (WHO) has prepared a number of recommendations for increased preparedness and research (42). The CHMP require pandemic vaccine to meet all the current evaluation criteria for marketing authorisation. They also recommend measuring neutralising antibodies, and suggest more detailed analysis of the immune response for example detection of antibodies directed against neuraminidase and cell mediated responses (43).

## Pandemic influenza vaccines

Parenterally administered inactivated influenza vaccines have been used for many decades and extensive information is available on their quality, safety and efficacy. These vaccines elicit an effective systemic immune response in individuals previously primed by natural infection but much less information is available on the immune response to influenza vaccines containing novel subtypes. During an influenza pandemic, vaccines will be a key intervention step in protecting the population. The type of vaccine, the amount of antigen, the route of administration, the number of doses and the incorporation of an adjuvant, in addition to the immunological status of the recipient, will all influence the immune response.

The use of a single dose regimen with a novel subtype is unlikely to be suitable in an immunologically naïve population, whereas a two dose regime more often results in seroconversion and fulfilment of the CHMP requirements (44)-(45, 46). The current influenza vaccine manufacturing capacity will not be sufficient to meet the global demand for a pandemic vaccine, particularly if two doses of vaccine are required to elicit an adequate antibody response (10, 46-50). Whilst whole virus vaccines have proved more immunogenic in unprimed adults than split or subunit vaccines (46, 51), most vaccine manufacturers are technically unable to convert their current split or subunit vaccine production process to whole virus production. Current seasonal influenza vaccines contain 15 µg HA from each of the three seasonal strains. In contrast, very high antigen doses (up to 90 µg HA) are required for non-adjuvanted split virus or recombinant pandemic H5 vaccines to elicit an antibody response sufficient to meet the CHMP criteria (10, 11).

Aluminium-salt adjuvants are readily available and inexpensive, and have been shown to modestly augment the antibody response after two doses of candidate pandemic influenza vaccines, either split (50) or whole virus formulations (44, 51). However, other trials found that aluminium adjuvant did not significantly enhance the antibody response to candidate H5 vaccines (49, 52, 53). The most promising adjuvants are the proprietary oil-in-water emulsion systems such as MF59, AS03 and AF03, which greatly enhanced homologous and cross reactive antibody responses after H5 vaccination (45, 48, 53-55) even at lower antigen concentrations (3.8 - 7.5 µg HA). There are more than 70 clinical trials of candidate pandemic influenza vaccines, which have been completed or are ongoing (56). To date pandemic influenza vaccines have been reported as safe and well tolerated, with most trials performed in healthy adults. A number of pandemic vaccines have met regulatory approval in Europe, the USA and Australasia including Pandemrix.

Most vaccine manufacturers are now producing pandemic influenza A (H1N1) 2009 vaccine and the first vaccines entered clinical trial in August 2009.

Importantly, the goal of pandemic vaccination is to elicit appropriate immunological effector mechanisms to reduce viral replication and thus viral shedding and provide protection against serious illness and death upon infection by pandemic influenza. Protective efficacy studies using pandemic candidate H5 vaccines in animal models have shown that correlates of resistance to serious illness and death to avian viruses may not be solely reflected by levels of circulating serum antibodies (30, 57-59). These findings raise concern about the use of the CHMP criteria for assessing surrogate correlates of protection to candidate pandemic vaccines and there is therefore a need for more research to allow a better understanding of the immune response after pandemic influenza vaccination in man.

The WHO has provided advice for deployment of pandemic influenza H1N1 vaccine which would ensure the integrity of the health-care system and the country's critical infrastructure; reduce morbidity and mortality; and reduce transmission of the pandemic virus within communities. The Norwegian Government has ordered enough pandemic A/H1N1 vaccine for two doses for the whole population. It is anticipated that the pandemic A/H1N1 vaccine should be licensed in October 2009 and the initial batches will arrive in Norway during October but delivery of all the vaccine will be staggered over time. One of the key groups of workers that will be prioritized for the first rounds of vaccination will be frontline healthcare workers. These workers are at increased risk of infection with influenza H1N1 and of transmitting that infection to susceptible patients. Thus, the potential advantages for healthcare workers are personal protection, protection of patients, and reduction of absenteeism.

There are five key criteria, which need to be addressed in clinical trials of pandemic influenza vaccines in man (60); 1) safety, 2) immunogenicity, 3) kinetics of the response, 4) long lasting immunity and 5) cross reactive immunity to influenza H1N1 strains. Furthermore, there is a clear need for improved understanding of the immune response elicited in human volunteers after vaccination with candidate pandemic vaccines including the quality and repertoire of the antibody response. These five criteria will be addressed in this trial as follows: The safety and tolerability of the H1N1 vaccine will be investigated by completion of a side reactions form detailing the local and systemic adverse reactions. The immunogenicity of the H1N1 vaccine will be assessed through the induction of local and systemic antibody and cellular immune responses. In a pandemic situation, an important aspect is the rapidity of the immune response to the H1N1

vaccine so the detailed kinetics of the immune response will be investigated. The capacity of the vaccine to elicit long lasting immunity and cross reactive immunity to H1N1 viruses will also be evaluated. Furthermore, the quality of the immune response induced by the vaccine will be studied. The study population of healthcare workers is a unique population as Bergen is one of the few places in the world that vaccinated before the peak of the pandemic activity allowing evaluation of the vaccine in an immunologically naïve population (61)

## **4. TRIAL OBJECTIVES AND PURPOSE**

The objectives and purpose of this trial are:

- 1) Evaluation of the local and systemic safety and tolerability of parenterally administered adjuvanted H1N1 influenza vaccine in all recipients of vaccine at Haukeland University Hospital.

To evaluate the immunogenicity of a pandemic H1N1 influenza vaccine including:

- 2) Provide a detailed time course of the immune response to vaccination with a novel influenza H1N1 virus including the kinetics of the T-cell, B-cell and antibody responses in up to 60 volunteers
- 3) Investigate the long-lasting immunity induced by the vaccine
- 4) Examine the ability of the vaccine to induce cross-reactive immunity to H1N1 strains
- 5) Evaluate the quality of the immune response induced by the vaccine.
- 6) Examine the immune response after seasonal influenza vaccination in this study population

## **5 TRIAL DESIGN**

### **1. A specific statement of the primary endpoints and secondary endpoints to be measured by the trial**

The primary endpoints of the trial are the local and systemic adverse events and tolerability of parenterally administered adjuvanted H1N1 influenza vaccine in all volunteers. The secondary

endpoints are the evaluation of the immunogenicity of adjuvanted H1N1 influenza vaccine and the ability of the vaccine to meet the CHMP evaluation criteria in a subset of volunteers.

The immunogenicity of the H1N1 vaccine will be assessed through the induction of specific local and systemic antibody and cellular immune responses, and analyses of the epitopes to which the response is directed. Furthermore, the capacity of the vaccine to elicit cross reactive and long lasting immunity will be evaluated. In a pandemic situation, an important aspect is the rapidity of the immune response to the H1N1 vaccine and therefore the detailed kinetics of the immune response will be investigated.

#### A description of the type/design of trial to be conducted

The clinical trial will be an open study, all subjects eligible for pandemic vaccination at Haukeland University Hospital will receive one dose of vaccine by intramuscular injection into the deltoid muscle. An adverse events form will be dispensed to all subjects.

In the immunogenicity study, blood and oral fluid samples will be collected at the appropriate days (e.g. 0, 7, 14 and 21) after pH1N1 and seasonal vaccination. This study is an open study and all subjects will receive the Pandemrix vaccine, however, the trial samples will be coded with a unique number. Serological assays will be conducted at The University of Bergen and also blinded by the reference laboratories, National Institute for Biological Standards and Control (NIBSC), Health Protection Agency (HPA) and University of Siena (UNISI). Blood samples will also be collected at 3, 6, 9, 12, 18 and 24 months after pH1N1 and seasonal vaccination. The kinetics of the immune response will be studied at the University of Bergen.

#### **2. A description of measure taken to avoid/minimize bias**

The study will be an open study. All trial blood samples will be coded and serological assays to be conducted at NIBSC, HPA and UNISI will be performed blinded.

#### **3. A description of the trial treatment and dosage and dosage regimen of the investigational medicinal product.**

Subjects will be immunised by intramuscular injection into the deltoid muscle with the pandemic A/H1N1 influenza according to national guidelines.

During the immunogenicity study up to 23 blood (by venepuncture) and 11 oral fluid samples will be collected at intervals after vaccination. The trial blood and oral fluid wash samples will be used to evaluate the antibody, T and B cellular responses induced after vaccination. The oral fluid sample will be collected using an absorbent pad placed on the gum to absorb the oral fluid for two minutes (Orasure™). Blood and oral fluid samples will be collected at appropriate days 0, 7, 14 and 21 after vaccination to allow investigation of influenza specific cellular and serum antibody responses after pH1N1 and seasonal vaccination, as previously described (21, 23, 25, 62-64). These samples will be allocated a unique subject identification number, and only information on the age; sex and previous influenza vaccination history of each subject will be available to the scientific research team. Serum samples will be analysed at the University of Bergen and also sent to the three reference laboratories in Europe for studying the antibody responses.

Sera will be separated from clotted blood samples and plasma will be separated from CPT herparinised blood, aliquoted and stored at -80 °C or -20°C for use in the HI, SRH, neutralisation assay, enzyme-linked immunosorbent assay (ELISA), HA protein array and other assays deemed appropriate. Lymphocytes will be separated from CPT herparinised blood samples and used directly in the relevant immunological assays e.g. enzyme linked immunospot assay (ELISPOT) and for evaluation of the B and T cellular responses by e.g. flow cytometry (FACS) and cytokine production by multiplex ELISA and FACS. The recently described novel approach using multifunctional T cells (e.g.  $\text{TNF-}\alpha^+\text{IFN-}\gamma^+\text{IL-2}^+$ ) will be used to evaluate the immune response after vaccination. This will allow evaluation of the quality or “multifunctionality” of the cytokine producing T cells induced after vaccination and has been found to be a better indicator of a protective T cell response than the magnitude of each cytokine response. Excess lymphocytes will also be stored in liquid nitrogen for use in relevant immunological assays e.g. *in vitro* activation assays at the University of Bergen.

#### Preparation and Administration

The vaccine will be administered by the Centre for Infection Prevention as part of Haukeland University Hospitals mass vaccination campaign against pandemic influenza A (H1N1) 2009 according to national guidelines.

Before use, the vaccine will be removed from the refrigerator and placed at room temperature for 5 and 10 minutes. The vaccine and adjuvant will be mixed according to the manufacturers instructions. Prior to injection, it will be gently shaken. The vaccine will be injected intramuscularly into the deltoid region (on the opposite arm to that of the blood sampling). To ensure intramuscular injection, the subject will be asked to relax and the needle will be inserted at the center of the deltoid muscle between the shoulder and axilla and between the back and front of the arm. Before injection, the syringe plunger will be drawn back in order to check that the injection is not administered intravascularly. All vaccinations will be recorded in PANVAK according to National guidelines and instructions from The Norwegian Institute of Public Health. The site and side of injection will be recorded for the subjects involved in the immunogenicity and kinetic studies in the patient information and in the case report form (CRF).

### **Precautions for Use**

Vaccination must not be performed in subjects allergic to any VACCINE component.

| Examine vaccination site
(30 minutes)  | ✓                    |       |        |          |          |          |           |           |           |
| Collection of Adverse Events               | ✓                    | ✓     | ✓      | ✓        | ✓        |          |           |           |           |
| Serious Adverse Events                     |                      |       |        |          |          |          |           |           |           |

The following blood samples will be collected:  
 Antibody studies (2 x 8mL clotted blood sample)  
 T- and B- cellular responses (4 x 8mL CPT™ heparinised)

**Figure 5.2.**

Flow chart of the immunogenicity study

[figure not shown]

## **STUDY PROCEDURE FOR SUBJECTS IN THE IMMUNOGENICITY AND KINETIC STUDIES**

### First visit: Day 0: First vaccination

Subjects will be enrolled following one to one interviews for immunogenicity and kinetic studies providing they meet inclusion and not meeting the exclusion criteria and give fully signed informed consent. The following procedures will then be carried out and recorded in the Case Report Form:

- Record personal details including age, sex, personal number
- Record relevant medical and medication history;
- Record influenza vaccination history;
- Allocate a unique subject identification number;
- Trial blood samples will be collected by venepuncture to measure the antibody, T- and B-cellular and antibody responses.
- An Orasure fluid sample will be collected to measure the local antibody response. The oral fluid sample will be collected using an absorbent pad placed on the gum to absorb the oral fluid for two minutes.
- Subjects meeting the inclusion and not meeting the exclusion criteria will be vaccinated parenterally (into the deltoid muscle of the upper arm (the opposite side to that used for venepuncture)). Vaccination will be recorded in PANVAK according to National guidelines. The side of injection will be recorded in the CRF
- Subjects will be observed for 30 minutes to check for immediate adverse reactions. Emergency equipment (adrenaline, corticosteroids) will be available in the event of a rare anaphylactic reaction to vaccine administration.
- The vaccination site will be examined for local reactions at the end of 30 minutes. These findings and any systemic adverse reactions will be recorded on the appropriate CRF page.
- Dispense the subject's adverse event forms to the subjects, and give instructions for its completion. The adverse event form must be returned to the site at the Day 21 visit.
- Each subject will be instructed in the evaluation of local and systemic adverse events.
- Schedule the next clinic visit.

Second visit: Day 7 ( $\pm 2$  day) post 1st vaccination

- The adverse event form will be reviewed.
- Trial blood samples will be collected by venepuncture to measure the antibody, T- and B-cellular and antibody responses.
- An Orasure fluid sample will be collected to measure the local antibody response.
- Schedule the next clinic visit.

Third visit: Day 14 ( $\pm 2$  days) post 1st vaccination

- The adverse event form will be reviewed.
- Trial blood and Orasure samples will be collected to measure the antibody, T- and B-cellular and local antibody responses respectively.
- Schedule the next clinic visit.

Fourth visit: Day 21 ( $\pm 4$  days)

During this visit the following will be carried out and recorded in the CRF;

- Collect and discuss Adverse Event Form.
- Obtain interim history, including post injection reactions, adverse events and use of prescription and relief medication
- Trial blood samples will be collected by venepuncture.

Fifth visit: 3 months ( $\pm 31$  days) post 2nd vaccination

- Subjects will be asked to give a trial blood sample.
- An Orasure sample will be collected.

Sixth visit: 6 months ( $\pm 31$  days) post 2nd vaccination

- Subjects will be asked to give a trial blood sample.
- An Orasure sample will be collected.

Seventh visit: 9 months ( $\pm 31$  days) post 2nd vaccination

- Subjects will be asked to give a trial blood sample.
- An Orasure sample will be collected.

Eighth visit: 12 months ( $\pm 31$  days) post 2nd vaccination

- Subjects will be asked to give a trial blood samples.
- Orasure samples will be collected.

Ninth visit: 18 months ( $\pm 31$  days) post 2nd vaccination

- Subjects will be asked to give a trial blood samples.
- Orasure samples will be collected.

Eleventh visit: 12 months ( $\pm 31$  days) post 2nd vaccination

- Subjects will be asked to give a trial blood samples.
- Orasure samples will be collected.

Laboratory Analysis for the immunogenicity study

The trial blood samples will be collected at appropriate days (e.g. 0, 7, 14 and 21) after pH11N and seasonal vaccination (as detailed below) and at 6-24 months post vaccination to be used in serological assays and to study the kinetics of the T- and B-cellular responses. The serological assays (HI, SRH and neutralisation assays) will be carried out at the reference laboratories the National Institute of Biological Standards and Control and Health Protection Agency, UK and, University of Siena, Italy according to established standard operating procedures (SOP). The kinetics of the immune response elicited after vaccination with a H1N1 vaccine, including initial HI assays, will be conducted using blood and oral fluid samples at the University of Bergen. The detailed immunological response will be studied using a variety of immunological methods e.g. serum antibody (HI, protein array, ELISA for antibody class and IgG subclasses, neuraminidase assays), peripheral blood antibody secreting cells (e.g. ELISPOT and non secreted IgG from B

cells), lymphocyte profiles (e.g. Flow Cytometry for multifunctional T cells) and cytokine producing T-cells (e.g. ELISPOT, ELISA, multiplex analysis). The long lasting and cross reactive immunity will be studied (National Institute of Biological Standards and Control and Health Protection Agency, UK, University of Siena, Mount Sinai, University of Bergen) using established appropriate immunological assays e.g. ELISA, HI, SRH, or FACS analysis of lymphocytes stimulated *in vitro* with different H1 strains. Sera may also be used in other serological tests deemed appropriate for detection of influenza specific responses e.g. western blots, pseudotype assays and epitope mapping using the phage display system.

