#### Kinetics of the immune response to inactivated influenza vaccine

Antibodies to the surface glycoproteins, HA and NA, of seasonal influenza strains are associated with resistance to infection, whereas antibodies to the conserved internal antigens, M and NP, are not protective (20). The cytotoxic T-cell response is mainly directed against the M and NP proteins and is important for clearance of the virus and recovery from illness.

Vaccination with inactivated vaccine results in both local and systemic responses. The serum antibody response increases as early as 2-6 days after influenza vaccination in primed subjects (21) and peaks at approximately 2 weeks after vaccination when 90% of vaccinees have protective antibody titres (21); (17). The serum antibody response then wanes over time and is generally two-fold lower 6 months after vaccination (22). A rapid increase in local secretory IgA antibody in the oral fluid is also observed after parenteral inactivated influenza vaccination but this antibody response only remains elevated for 3 weeks after vaccination (23, 24). Influenza-specific antibody-secreting cells (ASC) appeared earlier, at approximately 7 days post-vaccination, in the blood than serum antibody response (21) and consisted predominantly of IgG and IgA. In young children (2 to 3 years old), previous natural priming by influenza infection was essential to mount strong antibody and antibody secreting cell responses in the peripheral blood (25, 26).

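### Oral-fluid sampling is planned for Day 21, but the Day 21 visit procedures list only blood, so the local-antibody time course may have no sample between Day 14 and the 3-month visit

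*Protocol*

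**What the plan says.** Two places in Protocol Section 5 set the early sampling days for both specimen types. The description of the trial design says "blood and oral fluid samples will be collected at the appropriate days (e.g. 0, 7, 14 and 21) after pH1N1 and seasonal vaccination". Section 5.3, on the trial treatment and dosage regimen, says "Blood and oral fluid samples will be collected at appropriate days 0, 7, 14 and 21 after vaccination", this time without an e.g. Section 5.3 also gives totals per subject: "up to 23 blood (by venepuncture) and 11 oral fluid samples will be collected at intervals after vaccination".

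The study procedures for the immunogenicity and kinetic studies then go visit by visit:

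- **Days 0 and 7:** blood, and for oral fluid "An Orasure fluid sample will be collected to measure the local antibody response".
- **Day 14:** "Trial blood and Orasure samples will be collected to measure the antibody, T- and B-cellular and local antibody responses respectively".
- **Day 21 (fourth visit):** the adverse event form, an interim history, and "Trial blood samples will be collected by venepuncture". There is no oral-fluid line.
- **Every visit from 3 months on:** a blood sample and an Orasure sample.

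The background section on the kinetics of the immune response describes local IgA in oral fluid after earlier parenteral inactivated vaccines and notes that "this antibody response only remains elevated for 3 weeks after vaccination". Local antibody is part of the immunogenicity assessment in Section 5.1 and of the kinetic assessment in Section 8.1.

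**The concern.** The design text and the operational text disagree about one sample. The Day 21 list is introduced as what will be done and recorded in the CRF, so it is the text that clinic staff are most likely to work from. Nine of the ten listed visits have an oral-fluid sample, and no reason is given for leaving it out at Day 21. This looks like a drafting omission rather than a decision.

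At stake is the shape of the local-antibody curve after Day 14. If the sample is not taken, the data cannot show whether oral-fluid antibody is still raised at 3 weeks, and a sample not collected cannot be recovered. Section 5.4 says the schedule in Table 5.1 will be repeated with the trial's extension, so an uncorrected list could carry the gap into later rounds.

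**Working it through.** **1. Oral-fluid sampling by visit.**

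| Visit | Section 5 design text | Visit procedures |
|---|---|---|
| Day 0 | blood and oral fluid | blood and oral fluid |
| Day 7 | blood and oral fluid | blood and oral fluid |
| Day 14 | blood and oral fluid | blood and oral fluid |
| Day 21 | blood and oral fluid | blood only |
| 3, 6, 9, 12, 18 months and the visit headed Eleventh | oral-fluid days not named | blood and oral fluid |

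Day 21 is the only row where the two texts conflict.

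**2. Does other text settle it?** Table 5.1 has no Day 21 column and no oral-fluid row. The Day 21 window in Section 8.2 (deviations) is stated for blood sampling. Figure 5.2, the flow chart, is not reproduced in the text available, so nothing is inferred from it.

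**3. Count of oral-fluid samples.** The total stated in Section 5.3 is 11.

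- Visit list: 3 (Days 0, 7, 14) + 6 (later visits) = 9.
- With Day 21 added: 9 + 1 = 10.

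Neither count reproduces 11. The table of contents still shows an eleven-visit layout, which would give 11 at one sample per visit, but that this is the source of the figure is only an inference. Two of the six later visits (Eighth and Eleventh) carry the same 12-month label, so the count of six also rests on headings that need tidying.

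**4. Length of the gap if Day 21 is not sampled.** Inputs: Day 14 ±2; 3 months ±31 days; 1 month taken as 30.44 days, so 3 months = 3 × 30.44 ≈ 91.3 days. The visit list counts the 3-month visit from the second vaccination, whereas other sections describe one dose. Both anchors are therefore shown.

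| | Counted from Day 0 | Counted from a second dose at Day 21 |
|---|---|---|
| 3-month window | 91.3 ± 31 = about Day 60 to 122 | 21 + 91.3 ± 31 = about Day 81 to 143 |
| Nominal gap from Day 14 | 91.3 − 14 ≈ 77 days | 112.3 − 14 ≈ 98 days |
| Shortest gap (from Day 16) | 60.3 − 16 ≈ 44 days | 81.3 − 16 ≈ 65 days |
| Longest gap (from Day 12) | 122.3 − 12 ≈ 110 days | 143.3 − 12 ≈ 131 days |
| Nominal gap with Day 21 sampled | 91.3 − 21 ≈ 70 days | 112.3 − 21 ≈ 91 days |

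The Day 21 sample shortens the nominal gap by only 7 days. Its value lies in where it falls: at 3 weeks, the end of the period of raised local antibody reported in the background.

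**The case against.** The best defence is that Section 5.3 already instructs the same team, at one hospital programme, to collect oral fluid on Day 21, and that the flow chart may show the sample. Loss is therefore not certain. That stands: the sample is likely to be missed by anyone working from the visit list, but the documents do not show that it would be. The e.g. in the design description is not a defence, because Section 5.3 names Day 21 without it. A deliberate omission cannot be excluded either, though nothing in the text says so.

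A reader might also infer more than the documents support:

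- **That 11 against 9 is a counting error.** The words up to in Section 5.3 may govern both totals, making 11 a ceiling. The totals may also cover more than the single cycle in the visit list. Restoring Day 21 gives 10, so the count neither proves nor resolves the omission.
- **That the local sample paired with the CHMP serum is lost.** The CHMP criteria use serum HI or SRH only, and no paired oral-fluid and serum analysis is planned. Section 8.1 also evaluates the criteria at different time points, and Days 7 and 14 have both specimens.
- **That the protocol predicts a fall at Day 21.** The 3-week figure is background from earlier parenteral inactivated vaccines. No hypothesis, endpoint or analysis for this adjuvanted vaccine is tied to it.
- **That the gap is simply Day 60-122.** This assumes that 3 months runs from Day 0, which is not how the visit heading is worded.

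Finally, the methods in Section 8.2 describe the time course in terms of T-cell, B-cell and serum antibody responses. This limits the weight of local antibody, although Section 8.1 does include it in the kinetics.

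**Conclusion.** The inconsistency is real and minor. Section 5 plans an oral-fluid sample on Day 21, the Day 21 procedures omit it, and no other text shown resolves the conflict. If the visit list is followed, one of four early local-antibody points is missed. No sample would then fall between Day 14 and the 3-month visit, a nominal gap of about 77 or 98 days depending on the anchor, and the 3-week point would go unobserved.

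This rests on three assumptions: that staff work from the visit list, that a month is 30.44 days, and, for the longer figure, that a second dose falls exactly at Day 21. The consequence is limited to a component of a secondary endpoint. The primary safety endpoint and the three serum CHMP criteria are unaffected.

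**What to change.** Add the oral-fluid sample to the fourth-visit (Day 21) list so that it agrees with the design description and Section 5.3. If the omission was intended, say so in Section 5 instead. In the same edit:

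- Give Table 5.1 a Day 21 column and an oral-fluid row.
- Check the Section 5.3 total of up to 11 oral-fluid samples against the final schedule, and state which vaccination cycles it covers.
- Reconcile the reference point for the 3-month and later visits with the rest of the protocol, and resolve the duplicate 12-month label.

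The main change is one line. For the subject it adds a two-minute pad at a visit already attended for blood sampling, and the design text already plans for it.
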